## Abstract

**Background:**

University life typically occurs during a period of life transition, where the incidence of mental health and substance use problems and disorders peaks. However, relatively few students obtain effective treatment and support. e-Interventions have proven effective in improving the psychological outcomes of university students and have the potential to provide scalable services that can easily integrate into existing models of care. *Minder* is a mobile app codeveloped with university students that offers users a collection of evidence-based interventions tailored to help university students maintain their mental health and well-being and manage their substance use.

**Objective:**

This paper describes the protocol for a randomized controlled trial (RCT) that aims to assess the effectiveness of the *Minder* app in improving the mental health and substance use outcomes of university students.

**Methods:**

This study is a 2-arm, parallel assignment, single-blinded, 30-day RCT with 1 intervention group and 1 waitlist control group. Overall, 1496 (748 per trial arm) university students from the University of British Columbia Vancouver Campus (N=54,000) who are aged ≥17 years, have a smartphone with Wi-Fi or cellular data, and speak English will be recruited via a variety of web-based and offline strategies. Participants will be randomized into the intervention or control group after completing a baseline survey. Those randomized into the intervention group will gain immediate access to the *Minder* app and will be assessed at 2 weeks and 30 days. Those randomized into the control group will be given access to the app content after their follow-up assessment at 30 days. The primary outcomes are measured from baseline to follow-up at 30 days and include changes in general anxiety symptomology, depressive symptomology, and alcohol consumption risk measured by the General Anxiety Disorder 7-Item scale, Patient Health Questionnaire 9-Item scale, and US Alcohol Use Disorders Identification Test-Consumption Scale, respectively. Secondary outcomes include measures related to changes in the frequency of substance use, mental well-being, self-efficacy in managing mental health and substance use, readiness to change, and self-reported use of mental health services and supports (including referral) from baseline to follow-up at 30 days.

**Results:**

Trial recruitment and data collection began in September 2022, and the completion of data collection for the trial is anticipated by June 2023. As of May 10, 2023, a total of 1425 participants have been enrolled.

**Conclusions:**

The RCT described in this protocol paper will assess whether the *Minder* app is effective in improving the mental health and substance use outcomes of a general population of Canadian university students. Additional secondary outcome research aims to explore additional outcomes of interest for further research and better understand how to support students’ general mental well-being.

**Trial Registration:**

ClinicalTrials.gov NCT05606601; https://clinicaltrials.gov/ct2/show/NCT05606601

**International Registered Report Identifier (IRRID):**

DERR1-10.2196/49364

## Introduction

### Background

University represents a period of transition where many students move away from home for the first time, requiring them to navigate the newfound independence and overcome unanticipated challenges when trying to make new friends and preserve existing relationships [1-3]. Students may find themselves suddenly dealing with new stressors without their previously relied upon support systems [4]. These stressors related to university life are combined with a period of development where the onset of many mental health and substance use disorders peaks [5,6]. Certain individuals may also be more likely to experience mental health problems in university based on various factors such as age, sexual orientation, ethnicity, and adverse childhood experiences [7]. Overall, this results in a population with a relatively high prevalence of mental health and substance use disorders [8,9]. For example, a study of college students across multiple countries found the 12-month prevalence of major depressive disorder, generalized anxiety disorder, and alcohol use disorder to be 18.5%, 16.7%, and 6.3%, respectively [9]. Despite the high prevalence of emerging mental health and substance use concerns, many university students do not seek help for these issues [10,11].

e-Interventions that promote self-management and link students to in-person services represent a promising means of addressing needs related to substance use and mental health issues. The potential of digital mental health interventions (eg, web-based programs and mobile apps) has been widely promoted, as they are often easily scalable and as beneficial as in-person therapies in promoting university students’ mental health [12-14]. Considering the high co-occurrence between mental health and substance use concerns [15], e-interventions are well positioned to offer low-barrier access to content supporting transdiagnostic approaches to interventions that acknowledge not only each individual concern but also their intersectionality. Existing digital interventions also address a range of challenges, including depression and anxiety [16], substance use [17], safety and risk management [18,19], and levels of severity (eg, subclinical mild to moderate symptom management and treatment for clinical conditions), and can be easily integrated into existing systems of care as a form of low-intensity, self-directed support [20].

### Objective

To address these needs, a mental health and substance use mobile app called *Minder* was codeveloped with and for Canadian university students. This codevelopment process involved significant input from students through the creation of a Student Advisory Committee (SAC), usability testing via a virtual bootcamp (ie, individual user testing combined with a web-based survey), focus groups, and a pilot feasibility study [14]. By combining the prevention and early intervention components, the *Minder* app has been designed to target the general population of university students. This paper describes the protocol for a pragmatic 2-arm randomized controlled trial (RCT) to assess the effectiveness of the *Minder* mobile app in improving university students’ mental health and substance use outcomes.

## Methods

### Study Objectives and Hypotheses

Our primary objective is to test whether the *Minder* intervention improves mental health and substance use outcomes in a general population of university students. Our null hypothesis is that there is no difference between the intervention group, who are given access to a full version of the *Minder* mobile app, and the control group, who are given access to a restricted version of the app that sends reminder notifications about baseline and follow-up surveys but prevents access to all intervention components. We hypothesize that assignment to the intervention group will result in greater effects on the primary mental health and substance use outcomes. As such, we expect that participants assigned to the intervention group will be more likely to experience improvements in their mental health and substance use outcomes than those in the control condition.

### Study Design and Setting

The study is a single-blinded, 2-arm parallel assignment RCT with 1 intervention group and 1 control group (Figure 1). In the pretrial period (t−1), all students are screened for eligibility and invited to enroll in the study; enrolled participants then complete the baseline assessment survey (t0). After randomization, all participants enter into the trial (with full access or restricted access to the *Minder* app, depending on group assignment), concluding with a follow-up assessment survey at 30 days (t2; see Table 1 for participant flow through the study). In addition to the baseline and follow-up surveys, the intervention group will also complete an assessment at 2 weeks. The baseline and follow-up assessments contain all primary and secondary outcomes, whereas the 2-week survey contains only 2 primary outcome measures (Patient Health Questionnaire 9-Item [PHQ-9] and General Anxiety Disorder 7-Item [GAD-7]). All assessments are delivered through the app and typically require approximately 15 minutes to complete but may be completed at the participant’s own pace. The 30-day follow-up assessment may be completed for up to 14 days after the 30-day study period end point.

Upon the completion of the randomized controlled trial, participants in the control group will be offered access to the intervention for ethical reasons and will be followed (with those already in the intervention group) for up to 6 additional months as part of a separate period of natural observation not included in the formal RCT analyses. This trial was registered with ClinicalTrials.gov (NCT05606601) on November 4, 2022. The study will be conducted at the University of British Columbia (UBC), Vancouver Campus. All data will be collected in Canada.

**Figure 1 figure1:**
[figure not shown]
Outline of the trial process, including eligibility assessment, consent, baseline, randomization, and follow-up.

**Table 1 table1:** Participant flow through the trial.

			Enrollment (t−1)		Study period				
					Baseline assessment and allocation (t0)		Interim assessment (t1; 2 weeks)		Follow-up assessment (t2; 30 days)
**Enrollment**									
	Eligibility screen	✓							
	Informed consent	✓							
**Group allocation and assessment**									
	*Minder* intervention			✓		✓		✓	
	Control			✓				✓	
**Assessment measures**									
	Anxiety symptoms (GAD-7^a^)			✓		✓		✓	
	Depressive symptoms (PHQ-9^b^)			✓		✓		✓	
	Alcohol consumption risk (USAUDIT-C^c^)			✓				✓	
	Opioid use frequency			✓^d^				✓	
	Stimulant use frequency			✓^d^				✓	
	Cannabis use frequency			✓				✓	
	Alcohol binge frequency (question 3, USAUDIT-C)			✓				✓	
	Alcohol use frequency (questions 1 and 2, USAUDIT-C)			✓				✓	
	Mental well-being (SWEMWS^e^)			✓				✓	
	Readiness to change			✓				✓	
	Self-efficacy: mental health			✓				✓	
	Self-efficacy: substance use			✓				✓	
	Connection to services and supports			✓				✓	

^a^GAD-7: General Anxiety Disorder 7-Item.

^b^PHQ-9: Patient Health Questionnaire 9-Item.

^c^USAUDIT-C: US Alcohol Use Disorders Identification Test-Consumption Scale.

^d^Baseline measure used for study group allocation.

^e^SWEMWS: Short Warwick-Edinburgh Mental Wellbeing Scale.

### Eligibility Criteria and Assessment

Participant eligibility will be determined through an eligibility screener delivered on Qualtrics, a web-based survey platform, before registering for the study.

Participants must meet all the following inclusion criteria: student currently enrolled at the UBC Vancouver campus, aged ≥17 years, have access to and be able to use a smartphone with Wi-Fi or cellular data, and speak English. Students will be excluded based on an eligibility screening item assessing suicidality risk (“We want to make sure that this app is appropriate for you at this time. Do you have a current suicidal plan [i.e., a plan to end your life]?”). Anyone endorsing a current suicidal plan (ie, answering “yes”) will not proceed with the registration form and will instead be provided with a list of crisis resources.

### Intervention

*Minder* was codeveloped with input from 225 university students, including 44 student project team members. Codevelopment occurred through engaging students and volunteers on the project team, a SAC, and quantitative and qualitative studies (web-based survey, pilot feasibility RCT, and focus groups). Feedback was used to guide the app revisions following each of these processes, resulting in a final app that differed considerably from the initial prototype. Details of each component of these adaptation processes can be found in the study by Vereschagin et al [14].

*Minder* delivers a suite of evidence-based interventions that have been tailored to help university students improve their well-being and manage their substance use through 4 main components: Chatbot Activities, Services, Community, and Peer Coaching (Figure 2). The Chatbot Activities consist of an automated preprogrammed chatbot text and videos that draw primarily from cognitive behavioral therapy (CBT), given its demonstrated transdiagnostic efficacy in web-based intervention programs [21-24]. The Chatbot Activities also incorporate evidence-based content derived from metacognitive therapy, dialectical behavioral therapy, and motivational interviewing. These activities have been developed through collaboration with mental health professionals and university students so that the information can be presented in a way that is consistent with evidence-based practices and appropriate for this demographic. The Chatbot Activities were designed to support students on a range of topics and include content to manage mild to moderate distress and emotions and to help navigate general student life (eg, relationships, time management, and sleep hygiene). In addition, the content of the Chatbot Activities relates to the use of alcohol, cannabis, opioids, and stimulants, including general psychoeducation and motivational interviewing. These topics encapsulate many general skills included in CBT for managing emotions (eg, recognizing automatic thoughts) as well as additional topics highlighted by students through our codevelopment process as being more relevant to student well-being, such as transitioning to university. To increase the accessibility of the app, all activities that include video content have been closed-captioned in both English and French. Users have access to this entire range of content in the app and can choose to engage with any activities, regardless of their current mental health or substance use status. The Services component of *Minder* includes a validated psychosocial screening tool that provides users with tailored recommendations and resources based on their current needs and preferences [25]. It consists of a short survey with several categories (mental health, safety, substance use, abuse, housing, education, and sexual wellness) and an individually tailored list of relevant services that can be filtered by factors such as cost, availability, and delivery method. The Community component of *Minder* contains a searchable inventory of student groups or clubs at the university, which can be filtered according to the student’s interest. Finally, to support the use of the app, Peer Coaches (university student volunteers that have been trained by the research team’s clinicians) are available to help users navigate through different app components and provide nonclinical peer support. Once a Peer Coach is assigned, users can communicate with their coach through secure in-app texting or video calls in a synchronous or asynchronous manner. In this study, users in the intervention group will be offered Peer Coaches who will reach out to their assigned users twice during the study period (ie, at the beginning of the trial upon assignment and around the midpoint of the trial). Additional information on the development of *Minder* and its components can be found in the study by Vereschagin et al [14].

**Figure 2 figure2:**
[figure not shown]
Minder main app components. The Minder app home page has 6 islands (University life, Relationships, Stress and Anxiety, Wellness, Sadness, and Substance Use) that deliver a variety of activities through an interactive chatbot. The Services component includes a short survey that assesses needs and preferences and matches users with resources. The Community component provides users with a directory of student groups and clubs they can filter through by interest. The Peer Coaching component matches users with a trained peer that provides psychosocial and app support.

### Outcomes

#### Primary Outcomes

The primary outcomes are changes in general anxiety symptomology, depressive symptomology, and alcohol consumption risk from baseline to follow-up at 30 days.

##### Anxiety Symptoms

The GAD-7 scale is a commonly used self-report scale to assess symptoms of generalized anxiety. Questions on the scale draw from the Diagnostic and Statistical Manual of Mental Disorders, 4th edition [26], criteria for anxiety disorders and were formally validated against diagnostic psychiatric interviews [27]. Each question is scored from 0 (not at all) to 3 (nearly every day), with total scores ranging from 0 to 21 and higher scores indicating a worse outcome (ie, greater frequency of anxiety symptoms). In this study, changes in anxiety symptomology from baseline to follow-up at 30 days will be based on the GAD-7 total scores in both the intervention and control groups.

##### Depression Symptoms

The PHQ-9 scale is a self-report scale used to assess symptoms of depression and has been validated against diagnostic interviews administered by mental health professionals [28]. The 9 questions are based on the Diagnostic and Statistical Manual of Mental Disorders, 4th edition [26], diagnostic criteria for depressive disorders and scored on a scale of 0 (not at all) to 3 (nearly every day). The total scores range from 0 to 29, with higher scores indicating a worse outcome (ie, greater frequency of depression symptoms). In this study, changes in depressive symptomology from baseline to follow-up at 30 days will be based on the PHQ-9 total scores in both the intervention and control groups.

##### Alcohol Consumption Risk

The US Alcohol Use Disorders Identification Test-Consumption Scale (USAUDIT-C) is a 3-item self-report scale adapted from the consumption questions in the widely used Alcohol Use Disorders Identification Test (AUDIT). Compared with the AUDIT, the USAUDIT-C includes expanded response options for the first 3 AUDIT questions—from 5 to 7 categories—to allow for more precise measurements in accounting for differences in standard drink sizes and cut-off limits [29]. Although the USAUDIT-C was primarily adapted for US contexts, we believe the expanded response options will also allow for a more precise assessment of adherence to guidelines in drinking frequency (question 1), drinking quantity (question 2), and binge drinking (question 3) within Canadian contexts. For questions 1 and 3, scoring ranges from 0 to 6, where 0 represents “Never” and 6 represents “Daily” frequency. For question 2, scoring ranges from 0 to 6, where 0 represents “1 drink” and 6 represents “10 or more drinks” on a typical day when drinking. The total scores summed from all 3 questions range from 0 to 18, with higher scores indicating a worse outcome (ie, higher-risk level of excessive or harmful alcohol consumption). In this study, changes in alcohol consumption risk from baseline to follow-up at 30 days will be based on the USAUDIT-C total scores in both the intervention and control groups.

#### Secondary Outcomes

##### Overview

To provide further information on the underlying mechanisms and areas in which *Minder* is affecting participants’ overall well-being, a variety of secondary outcomes will be examined. Secondary outcomes include measures related to changes from baseline to follow-up at 30 days in the frequency of substance use (cannabis consumption, binge drinking, alcohol use, opioid use, and nonmedical stimulant use), mental well-being, self-efficacy managing mental health and substance use, readiness to change, and self-reported use (including referral) of mental health services and supports. An example of the questions used to assess secondary outcomes is provided in Multimedia Appendix 1.

##### Substance Use: Opioid Use Frequency

Changes will be based on the self-reported frequency of *both medical and nonmedical* opioid use in both the intervention and control groups.

##### Substance Use: Stimulant Use Frequency

Changes from baseline to follow-up at 30 days will be based on the self-reported frequency of nonmedical stimulant use in both the intervention and control groups.

##### Substance Use: Cannabis Use Frequency

Changes from baseline to follow-up at 30 days will be based on the self-reported frequency of cannabis consumption in both the intervention and control groups.

##### Substance Use: Alcohol Binge Frequency

Changes from baseline to follow-up at 30 days will be based on the responses to question 3 of the USAUDIT-C in both the intervention and control groups.

##### Substance Use: Alcohol Use Frequency

Changes from baseline to follow-up at 30 days will be based on the responses to questions 1 and 2 of the USAUDIT-C in both the intervention and control groups.

##### Mental Well-Being

Changes from baseline to follow-up at 30 days will be based on the total scores from the Short Warwick-Edinburgh Mental Wellbeing Scale in both the intervention and control groups. The Short Warwick-Edinburgh Mental Wellbeing Scale is a 7-item scale that has been widely validated, has strict unidimensionality, and is free from item bias [30]. The total scores range from 7 to 35, with higher scores indicating better outcome (ie, higher positive mental well-being).

##### Readiness to Change

Changes from baseline to follow-up at 30 days for the use of individual substances (alcohol, cannabis, opioids, and stimulants) will be based on self-reported readiness to change ladder assessments in both the intervention and control groups. The ladder assessments consist of a single item for each substance that asks participants to rate their readiness to change their use on a Likert-type response scale ranging from 0 (no thought of changing) to 10 (taking action to change). The response range parallels stages in the behavior change process from precontemplative to action stages, with higher scores indicating higher readiness to change and, therefore, a higher likelihood of changing their current substance use behavior. These questions were adapted from a readiness to change measure used by Merrill et al [31] to assess anticipated changes in alcohol use (adapted from The Contemplation Ladder, originally validated by Biener and Abrams [32]).

##### Self-Efficacy

Changes in mental health self-efficacy from baseline to 30-day follow-up are based on 5 survey questions in the intervention and control groups. Each question is scored separately using a Likert-type response ranging from 1 (not at all confident or likely) to 5 (totally confident or likely), with higher scores indicating a better outcome (ie, greater self-efficacy). Similarly, in both the intervention and control groups, changes in substance use self-efficacy from baseline to follow-up at 30 days will be based on 4 self-report survey questions assessing different aspects of self-efficacy related to substance use management. Each question is scored separately using a response ranging from 1 (not at all confident) to 5 (totally confident), with higher scores indicating a better outcome (ie, greater self-efficacy). Both the mental health and substance use self-efficacy survey questions were developed by the research team based on the theory of self-efficacy by Bandura [33].

##### Connection to Services and Supports

Changes in the use of mental health services and supports in both groups will be assessed by comparing responses to 2 yes-or-no survey questions from baseline to 30-day follow-up. The questions ask if participants have been diagnosed or treated by a professional for a list of mental health conditions and whether they have used any mental health treatments (medication, psychotherapy, mindfulness, and web-based tools) in the past 30 days or currently. Two additional survey questions are only asked at the 30-day follow-up: accessing types of support services and joining any university clubs or participating in any club-related events.

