### Randomization and Study Arms

A study participant is defined as an individual who has completed the baseline survey and has been randomly assigned into either the control or intervention group. Participants are randomized using a stratified block randomization function built into the app. The randomization list for the built-in function was created using the web-based stratified block randomization list creator in the clinical trial software Sealed Envelope (Clerkenwell Workshop) [35]. To ensure that each arm of the randomized trial contains an equal number of participants endorsing a history of substance use, participants will be assigned to either group A (substance use: any medical opioid use, nonmedical opioid use, or nonmedical stimulant use) or group B (nonsubstance use), based on their answers to the opioid and stimulant use questions in the baseline survey. After being stratified into group A or group B, individuals are then automatically randomly assigned (via the randomization list embedded into the app) to either the control or intervention arm of the trial using a 1:1 ratio in blocks of 10.

Those randomized into the control group will receive a message saying that they will be asked to complete an additional survey at 30 days and will only receive full access to the app after that. During the 30-day study period, the control group participants will receive a restricted version of the app that only permits access to the following: an introduction video with several students providing a broad overview of the different aspects of the app and its potential value, several onboarding slides with a short summary of the main app components, and baseline and follow-up assessment surveys plus reminder notifications to complete those surveys. Participants randomized into the intervention group will receive immediate access to the full *Minder* app.

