The general approach for analyzing all the types of study outcomes separately (including the 3 primary end points and the secondary end points) will be the generalized linear mixed-effect models (GLMMs) for clustered measures, with the randomization block as the clustering variable. These models can handle a wide range of outcome types, including continuous, binary, ordinal, and count, and can account for the correlations among observations within the same cluster. Specifically, we will analyze each primary end point using a linear mixed-effect model, a special case of the GLMM. For secondary outcomes, we will use linear mixed-effect models to analyze mental well-being measures and readiness to change measures, mixed logit models to analyze the connection to services and support-related measures (binary: yes or no), mixed-effects quasi-Poisson regression models with the log link (a special case of GLMMs) for substance use frequency measures, and mixed-effects proportional odds ordinal logistic regression (another special case of GLMMs) for self-efficacy measures. The treatment effect on an outcome at 30 days will be assessed using a GLMM with the treatment allocation as the main explanatory variable and with adjustment for baseline outcome assessment value and other baseline prognostic factors as fixed effects and the randomization block as a random effect. By properly specifying the GLMM, a wide range of scientific hypotheses can be tested, including the primary ones regarding treatment effect estimation. The quality of statistical inferences will be substantiated through rigorous model checking and validation techniques. When statistical models assume that residuals at certain levels follow normal distributions, this assumption will be checked using a normal probability plot, in which the ranked residuals are plotted against corresponding points on a normal distribution curve. When substantial departures from the normal residual assumption are found, robust empirical SE estimates that are valid with nonnormal residuals will be used for statistical inference. We will use SAS software (version 9.4; SAS Institute Inc) and R (version 4.3.1; R Foundation for Statistical Computing) for the statistical analyses of our primary and secondary outcomes. Subgroup analysis will be performed using the GLMM on the subsets of data formed by the subgroup.

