### Conclusions

Despite these limitations, the findings from this trial will inform the ongoing refinement of the *Minder* app. One key aspect of the *Minder* app that separates it from other similar tools is its extensive codevelopment process with students, especially in the development of content that is presented in a chatbot manner that is more interactive than other modular, web-based CBT interventions. It is designed to support a general population of students across many potential topics, whereas many existing tools target specific issues (eg, depression or anxiety). Thus, by designing a tool that can be used by all students, we hope to provide a suite of interventions (eg, from time management to managing emotions) that builds resilience across a range of conditions and improves the well-being of students as they face the many challenges associated with postsecondary education and young adulthood. This includes the tailoring and ongoing improvement of content using focus groups and continued engagement with specific groups of university students who may have more unique university experiences, including international students; lesbian, gay, bisexual, transgender, queer, 2-spirit, intersex, asexual, and similar minority (LGBTQ2IA+) students; and Indigenous and other racialized students. Through further analyses of app use data and subgroup analyses, we hope to identify areas of particular interest and need to help us better understand how to improve and scale up the delivery of the app to other student populations.

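### One service-use item counts web-based tools over the same 30 days in which only the intervention arm has the study app, so app use can score as treatment use in one arm

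*Protocol article*

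**What the plan says.** The Secondary Outcomes overview lists "self-reported use (including referral) of mental health services and supports" among the secondary outcomes. The section Connection to Services and Supports says that change will be "assessed by comparing responses to 2 yes-or-no survey questions from baseline to 30-day follow-up". The first of these items concerns diagnosis or treatment by a professional. The second asks "whether they have used any mental health treatments (medication, psychotherapy, mindfulness, and web-based tools) in the past 30 days or currently". Two further questions, on types of support service accessed and on student clubs, are put only at 30 days. Statistical Analysis assigns a mixed logit model to these binary measures, adjusted for the baseline value.

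On exposure, Randomization and Study Arms states: "Participants randomized into the intervention group will receive immediate access to the full" Minder app. The control version withholds every intervention component until the 30-day survey is done (Study Objectives and Hypotheses; Randomization and Study Arms). On content, the Intervention section describes "automated preprogrammed chatbot text and videos that draw primarily from cognitive behavioral therapy", and the Conclusions call the presentation "more interactive than other modular, web-based CBT interventions".

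**The concern.** The treatment-use item lists web-based tools as a kind of mental health treatment. The study app is a digital, CBT-based program that the article itself sets beside other web-based CBT interventions. A participant who used it could truthfully answer yes on that ground alone. Controls cannot, because they have no app content during the look-back.

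The item would then partly record whether people used what they were assigned. A higher yes rate in the intervention arm could arise with no change at all in use of outside services, and the model has no means of separating the two.

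**Working it through.** **The two windows.** The item looks back 30 days and the survey falls at day 30, so the look-back is the trial period. Study Design and Setting allows completion up to 14 days late. That moves the look-back by at most two weeks and still leaves it in intervention-only time, because controls gain access only after completing the survey.

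**Baseline adjustment.** The covariate is the same item answered before randomization, when nobody had the app. It cannot remove an exposure that begins after randomization in one arm.

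**Completers per arm.** The plan gives no figure for this outcome, so I take the evaluable number from Sample Size and Power (d = 0.2, 80% power, 0.05/3 = 0.0167, taken as two-sided):

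n = 2(z₀.₉₉₁₇ + z₀.₈)² / d² = 2(2.394 + 0.842)² / 0.04 ≈ 523.5, so 524 per arm, as stated. With 30% attrition, 524/0.7 = 748.6, against 748 stated.

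**Illustration.** Let p0 be the yes rate without the app and q the share of otherwise-no intervention participants who answer yes only because of it. The article gives neither; both are assumptions. With no true effect on outside services:

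- p1 = p0 + (1 − p0)q
- OR = [p1/(1 − p1)] / [p0/(1 − p0)]
- chance of significance in the app's favour = Φ[(p1 − p0 − 1.96·SE₀)/SE₁], with SE₀ pooled, SE₁ unpooled, 524 per arm and two-sided 0.05

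Example with p0 = 0.30 and q = 0.10: p1 = 0.30 + 0.70 × 0.10 = 0.37; OR = 0.587/0.429 = 1.37; SE₀ = 0.02916; SE₁ = 0.02908; (0.07 − 0.05715)/0.02908 = 0.44; Φ = 0.67.

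Each cell shows the intervention yes rate, the OR and the chance of significance:

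| p0 | q = 5% | q = 10% | q = 20% |
|---|---|---|---|
| 20% | 24%; 1.26; 35% | 28%; 1.56; 86% | 36%; 2.25; 100% |
| 30% | 33.5%; 1.18; 23% | 37%; 1.37; 67% | 44%; 1.83; 99.7% |
| 40% | 43%; 1.13; 16.5% | 46%; 1.28; 50% | 52%; 1.62; 97% |
| 50% | 52.5%; 1.11; 12.5% | 55%; 1.22; 37% | 60%; 1.50; 90% |

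At q = 0 the two-sided error stays at 5%. The calculation is unadjusted and ignores the randomization blocks.

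**The case against.** The strongest reply is that the article only paraphrases the items. Their wording is in Multimedia Appendix 1, which might exclude the study app or record each treatment type separately. This stands as a limit. It does not dispose of the point, because the outcome as the article defines it includes web-based tools and makes no exception for the app.

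It can also be said that the app need not count as a web-based treatment tool. The Background reads "The potential of digital mental health interventions (eg, web-based programs and mobile apps) has been widely promoted", which names web-based programs and mobile apps as separate examples, and some of the app's content, such as time management and the club directory, is hardly treatment. This is fair. It makes q uncertain, and q may be small, but the CBT content and the comparison in the Conclusions keep a yes answer reasonable.

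Three stronger readings are tempting, and the documents do not support them:

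- **Mindfulness.** A reader might infer that app use also scores under mindfulness. The Intervention section names CBT, metacognitive therapy, dialectical behavioral therapy and motivational interviewing, but not mindfulness.
- **A wrong conclusion on linkage.** A reader might infer that the trial would wrongly report that the app links students to services. The professional diagnosis-or-treatment item and the support-services item are not scored by app use, and nothing in the plan merges the items into one measure. That the outcome concerns services beyond the app is a natural reading of its heading, but the protocol does not state it.
- **A near-certain false positive.** The high figures hold only for larger q. At q = 5% the chance is 13-35%.

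**Conclusion.** The point holds for one of the two repeated yes/no items. As described, use of the study app can score as mental health treatment in the intervention arm only, so a difference on that item cannot be read as connection to outside services. The professional-treatment, support-services and club items are not affected in this way, and neither are the primary outcomes.

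The size cannot be known from the article. The figures rest on the assumed p0 and q and on 524 completers per arm. They show that a modest amount of such counting would be enough to matter, not that it occurs.

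**What to change.** Before unblinding, settle the scoring according to how the item was recorded:

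- If treatment types were recorded separately, score the item without web-based tools, for example on medication and psychotherapy, and report web-based tools descriptively.
- If only a single yes/no was recorded and its wording does not exclude the study app, treat the item as exploratory. Base any conclusion on linkage on the professional-treatment and support-services items.
- If the appendix wording already excludes the app, one sentence in the plan saying so closes the point.

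Do not reword the survey mid-trial. The abstract reports 1425 of 1496 participants enrolled by May 10, 2023, leaving 71 to enroll. New wording would reach few people, mix two versions of the item, and no longer match the baseline question used for adjustment.

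Rescoring needs no new data. Its cost is fewer events, and so less precision, in the narrower outcome.
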